#### 2.6.2. Objective 4: To develop and Optimize an HEP for Improving the Uptake of HIVST among Men in Rwanda

Design: Using the nominal group technique, purposive sampling will be done to recruit group participants. Individuals will be selected based on the researcher’s assessment that they will contribute to the adaptation of the HEP. A maximum of eight people is anticipated. Two staff from the HIV/AIDS and STIs Diseases Division of the Rwanda Biomedical Center at the national level, one representative each of a public and private health facility HIV department working in health promotion, and four representatives of the target population (men), purposively selected by the researcher. The principal investigator (first author) will serve as the convener and facilitator for the group. Guided by findings from the scoping review, by a qualitative study on the perspectives of key stakeholders, and by a cross-sectional survey on awareness and acceptability among men, information will be gathered by asking panel members to respond to questions posed by the moderator, and then by asking participants to prioritize the ideas or suggestions of each group member. The process is expected to prevent the domination of the discussion by a single person, encourage all group members to participate, and result in a set of prioritized strategies or recommendations that represent the group’s preferences for the HEP. Steps to be followed include introductions and explanations, a silent generation of ideas, sharing ideas, group discussion, voting, and ranking [31]. The increased number of heterogeneous inputs is expected to lead to quality decisions on key messages to prioritize for the HEP.

### 2.7. Recruitment Strategy

The principal investigator’s institution will send invitation letters to two purposively selected staff from the HIV/AIDS and STIs Diseases Division of the Rwanda Biomedical Center at the national level and one representative each of a public and private health facility HIV department working in health promotion. We will consult sector and cell leaders to enroll four representatives of the target population (men).

### 2.8. Inclusion Criteria

For this objective, we will enroll personnel employed by HIV/AIDS and STIs Diseases Division at the Rwanda Biomedical Center at the national level, or personnel employed by a public and private hospital and responsible for HIV services and health promotion as subject matter experts. Men over the age of 18 residing in Nyarugenge will be eligible as representatives of the target population.

Data Source: Data will be obtained from the transcripts.

Analysis: We will audiotape and transcribe the nominal group meeting. We will group related ideas to form themes. The themes will be ranked and prioritized. The ranking score will be between one and five, one being the least severe and five being the most severe barrier to the uptake of current HTSs. Thereafter, stakeholders will discuss key messages to include in the HEP to address each barrier. The panel members will receive a summary of the formulated HEP for validation.

Outcome: An adapted and optimized HEP tailored implementation strategy, likely to be effective for improving the uptake of HIVST among men in Rwanda, will be designed.

### 2.9. Phase 4: Pilot Randomized-Controlled Trial

Objective 5: HIVST was officially introduced on World AIDS Day in 2017 in Rwanda [46]. Since then, HIVST guidelines have been included in the national HIV prevention and management guidelines as of 1 July, 2018 [47]. Available evidence show a lack of awareness of HIVST among men in Kigali [28]. In this phase, we will aim to determine the preliminary effectiveness of the HEP on the uptake of HIVST among men in Rwanda and assess the feasibility of conducting a larger trial.

Design: The pilot RCT protocol is registered with the Pan African Clinical Trial Registry (Registration: PACTR201908758321490). We will conduct a two-arm pilot RCT. Participants will be randomized to the HEP arm or the control arm. In the control group, routine health education will be administered. In the intervention group, the adapted HEP will be administered in addition to routine health education. Data collection will be through interviewer-administered questionnaire captured onto mobile tablet devices using pre-programmed study software Open Data Kit.

Recruitment strategy: The University Teaching Hospital of Kigali (CHUK) will be purposively selected to pilot the implementation of the HEP intervention. CHUK is the largest hospital located in the district of Nyarugenge, Kigali. It is also the largest referral hospital in the country with a capacity of 519 beds. In 2017, the hospital recorded 140,559 patients with an average of 11,713 per month [11]. The PI of the study will introduce the intervention in the out-patients’ department, as these individuals are not expected to have critical conditions that would affect their ability to take part in the HEP or the interviewer-administered questionnaire. Trained health care professionals will administer the HEP to eligible participants. In this study, we will include participants who fit the following criteria:is an adult man 18 years and older;does not know his HIV status;is visiting the study-selected health facility during the enrollment periodis willing to be followed up three months post-enrollment.

Intervention: The intervention will be presented at the end of Phase 3 of the study. It will be a male-tailored HEP aimed at improving the uptake of HIVST among men. This will be delivered through face to face personal communication with the use of information education communication materials. We anticipate the HEP to address general information on HIV, transmission, prevention, HIVST, anti-retroviral therapy, and care in a manner that is tailored to men.

Randomization procedure: Simple randomization using a randomization table created by a computer software program will be employed.

Blinding: For the purposes of this study, there will be no masking. 

Data Source: We will employ an interviewer-administered questionnaire to collect data.

Analysis: Proportions will be calculated for the uptake of HIVST for both control and intervention groups. KAP scores will be calculated by determining the average score for each individual for each category of KAPs that will be assessed. Tables and graphs will be used where appropriate to present results. Quantitative variables will be summarized by means and standard deviation (SD). Qualitative variables will be summarized using frequency distribution. The student t-test or analysis of variance (ANOVA) will be used to compare if there are differences in KAP scores between different categories of the factor variables. Linear regression will be utilized to determine the association between KAP scores and quantitative factor variables. Multiple logistic regression will be used to determine the association between the uptake of HIVST and the use of HEP whilst adjusting for other study variables. All statistical tests will be concluded at a 5% level of significance. All statistical analysis will be carried in the Stata version 16 statistical package.

Primary outcome(s): The feasibility of a larger RCT trial will be assessed by recruitment and the uptake of HIVST Uptake of HIVST will be measured as self-reported use of a HIVST kit at follow-up interview. 

Secondary outcome(s): Secondary outcome variables will include HIV diagnosis among participants, linkage to care for men who tested positive for HIV, a repeat test from men who tested negative for HIV, and HIV status disclosure to sexual partner(s) post-HIVST.

Table 3 summarizes the outcomes, exploratory factors, and the methods of analysis for each study objective.

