## 4. Discussion

The aim of this study is to adapt an HEP for improving the uptake of HIVST by men in Rwanda. To the best of our knowledge, this study is the first of its kind in Rwanda. Given the reported low uptake of HTSs among men in Rwanda, and in Sub-Saharan Africa in general, implementing an effective HEP to improve the uptake of HIVST, a new intervention with reported acceptability among men, may help bridge this gap. The pragmatic approach is designed to provide results that are directly applicable to normal practice.

Several studies have called for the need for the implementation of policies that advocate for men’s health [49,50,51]. Tailored HEPs to improve men’s uptake of HTSs have been recommended [52]. As HIVST is relatively new in Rwanda [11], there is need for the implementation of guidelines and policies that advocate for men’s engagement in this new intervention and for the scaling up thereof [53]. The knowledge obtained by the present study may thus guide HIVST implementation in Rwanda with the potential of being further incorporated into routine practice.

Consistent with the nature of pragmatic trials, we aim to influence policy by providing stakeholders with results that are applicable to routine practice. We intend to disseminate findings of the study through reports, publications in peer-reviewed journals, research meetings, and conference presentations.

Due to constraints of time and resources, as this study is for a doctoral degree with limited findings, a pilot RCT will be used to assess the preliminary effects of the HEP. A pilot study is not a hypothesis testing study. However, a pilot study is a requisite initial step, and results can inform feasibility and identify modifications needed in the design of a larger ensuing hypothesis-testing study. In this study, the feasibility of recruitment, intervention implementation, and retention will be examined. Secondly, due to the nature of the HIVST being conducted privately, study outcomes will be based on self-reported data. Finally, the HIVST uptake is only as important as the number of individuals actively linked to care and treatment services. The proposed study will not actively follow up on participants for linkage to care and treatment services. However, sufficient information on linkage to care post-HIVST will be provided on both enrollment and follow-up visits.

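### The pilot waives masking for every role, including the follow-up interviewer who records self-reported kit use, so interviewer knowledge of the arm can add differential over-reporting to the uptake result

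*Protocol article*

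**What the plan says.** All references are to the protocol article.

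- **Masking (section 2.9):** "For the purposes of this study, there will be no masking". No role is excepted and no reason is given.
- **Primary uptake outcome (section 2.9):** "Uptake of HIVST will be measured as self-reported use of a HIVST kit at follow-up interview".
- **Mode (section 2.9):** "Data collection will be through interviewer-administered questionnaire captured onto mobile tablet devices", and again "We will employ an interviewer-administered questionnaire to collect data".
- **Arms and delivery (section 2.9):** "In the intervention group, the adapted HEP will be administered in addition to routine health education". On who delivers it: "Trained health care professionals will administer the HEP to eligible participants". The article does not say who conducts the follow-up interviews, or whether those people also deliver the HEP.
- **Use of the outcome:** section 2.9 relates uptake to the HEP by multiple logistic regression, with tests at the 5% level. Table 3 sets two success criteria, 60 men followed at three months and at least 80% taking up self-testing.
- **Acknowledged limitation (section 4, Discussion):** because self-testing is private, "study outcomes will be based on self-reported data". Reporting that differs by arm, and the interviewer's knowledge of the arm, are not mentioned.

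**The concern.** The HEP is face-to-face communication meant to raise uptake of self-testing. Three months later the same man is asked whether he self-tested, and the person asking may know that he received the HEP. Nothing stated in the plan limits arm-dependent prompting, probing or coding of the answer.

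Participants and educators cannot be masked to an education session. The follow-up interviewer can be, at least in principle, yet the waiver covers that role too. The private nature of testing explains why use is reported rather than observed. It does not explain why the interviewer needs to know the arm.

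Two results rest on this single answer: the between-arm contrast that is to show preliminary effectiveness, and the 80% criterion. If over-reporting is more frequent in the HEP arm, the contrast is biased in favour of the HEP and the criterion becomes easier to meet.

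**Working it through.** The article gives no figure for reporting error, so there is nothing to reproduce. The following is an illustration only.

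**Inputs from the article:** 60 men followed at three months and an 80% uptake criterion (Table 3); two arms with simple randomization (section 2.9).

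**Assumptions:** 30 men per arm, since neither the allocation ratio nor the split is stated; the same true uptake p in both arms, so no HEP effect; a share r of non-users who claim use, which may differ by arm. Every value of p and r is assumed.

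**Step 1: bias in the contrast.** Reported uptake = p + (1 − p) × r. Spurious difference = (1 − p) × (r_HEP − r_control).

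- Central case, p = 0.60, r = 0.20 against 0.05: HEP 0.60 + 0.40 × 0.20 = 0.68; control 0.60 + 0.40 × 0.05 = 0.62; difference +6 points.
- Low end, p = 0.70, r = 0.10 against 0: 0.30 × 0.10 = +3 points.
- High end, p = 0.50, r = 0.30 against 0.10: 0.50 × 0.20 = +10 points.

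**Step 2: effect on a 5% test.** Exact enumeration with p = 0.50, 30 per arm and a Pearson chi-square test:

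| r, HEP vs control | Reported uptake | Rejection rate |
|---|---|---|
| 0 vs 0 | 50% vs 50% | 5.2% |
| 0.20 vs 0.10 | 60% vs 55% | 6.8% |
| 0.20 vs 0 | 60% vs 50% | 12.3% |

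Small differential reporting hardly moves the test; larger differences do.

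**Step 3: effect on the 80% criterion.** Table 3 does not say whether it applies to the HEP arm or to all men, so both are shown. Take p = 0.70 and r_HEP = 0.30, giving reported uptake of 0.70 + 0.30 × 0.30 = 0.79 in the HEP arm.

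- HEP arm only, at least 24/30: P = 0.160 at 0.70 and 0.553 at 0.79, so 16% becomes 55%.
- All men, at least 48/60, with no over-reporting: P = 0.057.
- All men, r_control = 0 (arms at 0.79 and 0.70): P is about 0.20.
- All men, r_control = 0.10 (arms at 0.79 and 0.73): P is about 0.29.

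**Step 4: what masking would remove.** All of these figures are total over-reporting. It has an interviewer part and a participant part, and nothing in the article separates them. The reduction from masking the interviewer therefore cannot be computed.

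**The case against.** The strongest reply has four parts.

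1. **Self-report is already disclosed, and the Discussion says a pilot does not test hypotheses.** This lowers the consequence but does not remove the point. The plan still aims at preliminary effectiveness, tests at 5%, and sets a numerical uptake criterion. The disclosure concerns self-report, not who knows the arm.
2. **Most of the bias may come from the men themselves.** Men who have been taught to self-test may give the welcome answer to anyone. This stands: masking the interviewer leaves it in place.
3. **Masking may not be free.** The Discussion cites limits of time and resources in a doctoral study. A reader might infer from the separate mention of health professionals and interviewers that these are different people, so that masking needs no staff. The article does not say so. If one small team does both jobs, the roster may need more people.
4. **The figures depend on assumed rates.** This stands as well. A reader might go further and apply 30% over-reporting to all 60 men, which takes the chance of at least 48/60 from 6% to 50%. That is not the mechanism at issue, because both arms then over-report equally. When reporting differs by arm, the figure is about 20% to 29%.

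**Conclusion.** The point holds in a limited form. Section 2.9 waives masking for all roles, gives no reason for including the interviewer, and rests the primary uptake outcome on an answer given to that interviewer. This is a stated design rule, not a detail left for a fuller document.

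Under the assumptions above, a bias of 3 to 10 points in the contrast is possible, together with a material rise in the chance of meeting the 80% criterion. Neither is shown to occur. The documents do not support the inference that masking the interviewer would remove all of this, or that it would certainly cost nothing. The point is a worthwhile, inexpensive improvement to a pilot that is meant to inform a larger trial, and not a flaw that invalidates it.

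**What to change.** Replace the blanket waiver in section 2.9 with a statement by role, and add three form-level safeguards:

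1. Participants and educators are unmasked. Interviewers at three months are masked to arm where existing staffing allows, and nobody interviews a man to whom they delivered the HEP.
2. Allocation is left off the follow-up Open Data Kit form.
3. The kit-use item comes before any item that reveals exposure to the HEP.
4. The man enters that one item on the tablet himself, with help on request.

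**Cost:** items 2 to 4 are wording and form settings on tablets already planned, with no added staff. Item 4 is a small departure from the interviewer-administered mode and should be described as such. Item 1 depends on staffing that the article does not describe.

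**Downsides:** some men will reveal their arm during the interview, some will need help with self-entry, and over-reporting that comes from the participants is not removed by masking the interviewer. The report should say so when it presents the uptake contrast.

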**Phase 4: Objective 5 To determine preliminary impact of the HEP on uptake of HIVST among men in Rwanda**			
- Recruitment - Uptake (self-reported use of the HIVST kit)	- 60 men followed after 3 months - At least 80% will take up HIVST	- Percentage response rate - Proportion of men who will take up HIVST	Descriptive statistics or estimates based on 95% confidence intervals (CI)
% of men who get HIV diagnosis	Higher proportion of HIV diagnosis, linkage to care, and repeat testing for negative participants in the intervention group (HEP), compared with the non-intervention group.	Age, education level, religious belief, sexual behavior, sexual preference, marital status; age of first sexual encounter; the number of sexual partners, the history of STI, circumcision, condom use, alcohol and drug use, perceived risk of contracting HIV, level of income, distance to the point of sale of HIVST	Logistic regression
% of men who tested HIV positive and linked to care			
% of repeat test from men who tested HIV negative			

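### Section 2.9 sets a 5%-level logistic regression of HIVST uptake with an open covariate set, against Table 3 and the Discussion; about 60 men could not support a long adjustment list

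*Protocol article*

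**What the plan says.** All references are to the Protocol article.

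- **Section 2.9, Analysis.** Uptake proportions are calculated for each group. A multivariable model is added: "logistic regression will be used to determine the association between the uptake of HIVST and the use of HEP whilst adjusting for other study variables". The other variables are neither named nor limited in number. The same paragraph adds: "All statistical tests will be concluded at a 5% level of significance".
- **Section 2.9, Primary outcome(s).** Recruitment and self-reported uptake are the primary outcomes, used to judge feasibility.
- **Table 3, Objective 5, recruitment and uptake row.** The method is "Descriptive statistics or estimates based on 95% confidence intervals (CI"; no regression appears. The success criteria are "60 men followed after 3 months" and "At least 80% will take up HIVST".
- **Table 3, Objective 5, secondary-outcome rows** (HIV diagnosis, linkage to care, repeat testing). The method is logistic regression, with directional hypotheses and 15 factors. The list opens with "Age, education level, religious belief, sexual behavior, sexual preference, marital status; age of first sexual encounter; the number of sexual partners, the history of STI" and continues with six more.
- **Section 4, Discussion.** "A pilot study is not a hypothesis testing study". It adds that pilot results can inform the design of a larger study.

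**The concern.** One primary outcome has two descriptions of its analysis. Section 2.9 has an adjusted model judged at 5%; Table 3 has estimation only; the Discussion supports Table 3. An analyst could follow either, and a later analysis plan would inherit the conflict.

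The choice matters because the adjusted model has no limit on its covariates. With few men and high expected uptake, non-users are the limiting outcome. A long covariate list would then push the maximum-likelihood odds ratio away from 1 and sometimes leave it without a finite value. A 5% test on about 30 men per arm would also often miss a difference worth pursuing. A reader planning the larger trial could be misled by an inflated odds ratio or by a non-significant result.

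**Working it through.** **Plan's own figure.** No sample-size derivation is given for Phase 4, so there is nothing to reproduce.

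**Inputs from the document.** 60 men followed and uptake of at least 80% (Table 3); 15 factors (Table 3, secondary outcomes); 5% level (section 2.9).

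**Assumptions.** 60 is the total over both arms (120 in total is shown as the alternative). Allocation is 1:1. Tests are two-sided. The 15 factors enter the uptake model with one parameter each. Control uptake is not given, so a range is used.

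**Step 1: events per parameter.** Formula: min(users, non-users) / (15 covariates + 1 arm term).

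- 60 men, 80% uptake: 60 × 0.20 = 12 non-users; 12/16 = 0.75.
- 60 men, 50% uptake: 30/16 = 1.9.
- 120 men, 80% uptake: 24/16 = 1.5.
- 120 men, 50% uptake: 60/16 = 3.75.

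Factors with several categories would lower these values.

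**Step 2: behaviour of the adjusted odds ratio.** Logistic models were simulated with independent noise covariates. A fit was unusable if it did not converge, had a coefficient above 15 in absolute value, or had a standard error above 50. True odds ratios: (0.9/0.1)/(0.7/0.3) = 3.9 and (0.8/0.2)/(0.6/0.4) = 2.7. Ranges are over repeat simulations of 1,000 to 2,000 replicates.

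| Men | Covariates | True uptake | True OR | Median OR in usable fits | Unusable |
|---|---|---|---|---|---|
| 60 | 15 | 70% vs 90% | 3.9 | 8.3 to 9.4 | 19% to 23% |
| 60 | 15 | 60% vs 80% | 2.7 | 4.5 to 4.6 | 2% to 3% |
| 60 | 2 | 70% vs 90% | 3.9 | 4.0 to 4.3 | 4% to 5% |
| 60 | 2 | 60% vs 80% | 2.7 | 2.8 | under 1% |
| 120 | 15 | 70% vs 90% | 3.9 | 5.1 to 5.4 | 0.1% |
| 120 | 15 | 60% vs 80% | 2.7 | 3.1 to 3.2 | 0% |

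Inflation with 60 men and 15 covariates is 4.5/2.7 = 1.7-fold to 8.3/3.9, about 2.2-fold, and slightly more in some repeats. With 120 men it is about 1.2- to 1.4-fold. With two covariates it is at most about 1.1-fold. The remaining 4% to 5% of failures at 70% vs 90% come mostly from an arm with no non-users (0.9^30 = 4%), not from adjustment.

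With no true effect, 80% uptake, 60 men and 15 covariates, the median standard error of the log odds ratio was 1.08, against 0.67 unadjusted. The nominal 5% test rejected in about 8% of usable fits.

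**Step 3: the 5% test without adjustment.** Power of the pooled z-test with 30 per arm, against 80% uptake:

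- control 70%: 14%
- control 60%: 39%
- control 50%: 69%
- control 40%: 91%

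With 60 per arm, power for 60% vs 80% is 68%.

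**Step 4: what estimation gives instead.** For 24/30 vs 18/30 the difference is 20 percentage points, with a Newcombe 95% CI of about −3 to +41. That states the uncertainty plainly.

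**Step 5: the secondary outcomes.** As an illustration, the 6.0% male prevalence quoted for Nyarugenge in section 2.3 gives 60 × 0.06 = 3.6, about 4 HIV-positive men, for a regression with 15 factors. Prevalence among men who do not know their status may differ.

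**The case against.** The strongest reply is that Table 3 does not assign the 15 factors to uptake. They stand with the secondary outcomes, and naming covariates can properly be left to an analysis plan. This stands: a reader might infer that section 2.9 specifies a 15-covariate uptake model, but the document does not say so. With two covariates the inflation and most of the failures go. What remains is that section 2.9 sets no limit and that these are the only factors the article lists for regression in Phase 4.

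Other replies also have force:

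- **The two analyses are not mutually exclusive.** Section 2.9 also reports proportions by group, so the regression is an addition. Table 3 is a summary and itself plans regressions for secondary outcomes, so the document is not descriptive throughout. The conflict is therefore confined to the 5% adjusted test of uptake.
- **0.75 is not an upper bound.** It holds at 80% uptake, which is a success criterion and not a forecast.
- **60 is a follow-up criterion and may be per arm.** At 120 men the fits rarely fail, although some inflation remains.
- **Low power depends on control uptake.** A reader might infer that the test would mostly fail; at 40% vs 80% it would not.
- **Feasibility is judged on 60 followed and 80% uptake.** No text says that the adjusted odds ratio will size the larger trial.

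A reader might also take the exposure wording, which names use of the programme, as planning an as-treated comparison. Section 2.9 randomises to two arms and reports by group, so that reading is speculative.

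**Conclusion.** The point holds as an inconsistency that should be fixed. Section 2.9 puts a 5%-level adjusted test on a primary outcome for which Table 3 gives estimates only, in a study that the Discussion says does not test hypotheses. This part needs no assumption.

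The size of the harm is conditional. It reaches a 1.7- to 2.2-fold inflation or slightly more, with about 3% to 20% unusable fits, only if 60 is the total and all 15 factors enter the uptake model. It falls to about 1.2- to 1.4-fold with 120 men and largely disappears with two covariates. The simulated figures assume independent covariates and the uptake values shown. The documents do not support the stronger claim that the planned model cannot be estimated.

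**What to change.** - In section 2.9 and in the uptake row of Table 3, give one main analysis: the uptake proportion by randomised arm, with an unadjusted risk difference and 95% CI (for example Newcombe). Table 3 does not yet state a by-arm difference, so it needs the addition too.
- For Phase 4 uptake, drop the 5% significance criterion.
- If an adjusted model is kept, label it exploratory, limit it to one or two baseline covariates named in advance, and use Firth penalisation.
- Apply the same limit to the 15-factor logistic regressions that Table 3 plans for the sparser secondary outcomes.
- Optionally, describe the exposure as randomised arm, for clarity.

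The cost is a change of wording, with no effect on participants or data collection. The fully covariate-adjusted association is given up.
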